### Outcomes

In each center, both randomized groups are assessed for the outcomes listed below by standardized methodological procedures and a similar schedule (Table 3). Outcomes are measured for all randomized participants, irrespective of attendance or completion status. For participants who drop out of the study at any time after the randomization, research personnel use contact information to invite such individuals to undergo the end-study outcome assessments (12 weeks after intervention onset).

**Table 3 Tab3:** Time scheme for study conduction

	Study period							
	Enrolment	Baseline measures	Allocation and run-in^*^	Post-allocation			Close out	
TIMEPOINT**➔**	t-1	t0	t1	t2	t3	t4^†^	t5^†^	t5^†^
*Timepoint description*	Interviews	Occurs in 2 or 3 evaluation visits	–	Intervention Start	Evaluation visit (6th week)	Intervention end	Final evaluation visit 1	Final evaluation visit 2
ENROLMENT:								
Eligibility screening	x							
Informed consent	x							
Allocation			x					
INTERVENTIONS								
Combined exercise program				x	x	x		
Health education program				x	x	x		
ASSESSMENTS								
*Primary outcome*								
Ambulatory blood pressure		x					x	
*Main secondary outcomes*								
Office blood pressure		x					x	
Endothelial function^‡^		x			x		x	
Cardiorespiratory fitness^§^		x						x
*Other outcomes*								x
6-min walking test distance		x						x
SPPB		x						x
Quality of life questionnaires		x					x	
Autonomic function^‡^		x					x	
*Additional measurements*								
Anthropometric measurements		x					x	
Medication adherence scale (MMAS-8 Questionnaires)		x					x	
Blood variables collection		x					x	
Self-reported physical activity		x			x		x	
Grip strength		x			x			x

*SPPB* Short physical performance battery; *MMAS* Morisky Medication Adherence Scale. * = run-in period will be no longer than 2 weeks. † = time between t4 and t5 will be no longer than 2 weeks. ‡ = analysis of blood pressure and heart rate variability, exclusive for data collected at the coordinator center; § = cardiorespiratory fitness assessment occurs in a third separate visit at the participating center. Use of the©MMAS is protected by US copyright and registered trademark laws. Permission for use is required. A license agreement is available from [name], [name]; [contact]

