#### Primary outcome

The primary study outcome is systolic BP assessed by 24 h ambulatory BP monitoring measured before and after three months of intervention. Systolic BP was chosen as the primary outcome due to its linear rise in relation to age and powerful prediction of cardiovascular events in older adults [15, 16]. The study timeframe was chosen to allow an adequate time range to effects (if any) take place, while optimizing trial logistics and participants adherence to interventions [7].

The ambulatory BP values will be treated as individual values for diurnal (from device placement to 10 PM, within the evaluation day), nocturnal (from reported sleep time to reported waking time) and 24 h periods, aggregated as group means at baseline and 12 weeks (trial end). Baseline measurements are carried out no longer than 30 days before the first intervention session whereas post-intervention assessment occurs within 10 days after the last session.

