### Data collection

A manual of operating procedures (MOP) was written to increase the consistency for implementation of assessments and interventions across the two study centers. In addition, standard operating procedure (SOP) documents are available for each assessment. Outcome assessors were trained and the handling of a SOP short version is mandatory during each data collection. A data collection committee formed by members of the two centers gathered before the trial onset to consolidate data collection procedures between centers. Periodic meetings and written communication are established to promote internal transparency and consistency.

All variables are assessed at baseline (prior randomization) and at study completion, whereas endothelial function, self-reported physical activity and handgrip strength are additionally assessed at the 6th week of intervention. A participant timeline for the study is presented in Table 3.

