Incomplete data will be explored in sensitivity analyses by pattern mixture model. This procedure will describe whether there is an interaction between the main missing patterns and other variables (e.g., group, time, group by time, BP status, BP status by group). We expect two main missing data patterns based on an indicator of completers versus non-completers (defined as randomized subjects without 12-week data). Because withdrawals may occur due to specific harms or other non-anticipated reasons, we will assess whether additional grouping (indicator) should be made due to different patterns of missing data. Therefore, we will qualitatively document reasons and details of withdrawals on a case-by-case basis. In the case of identifiable patterns indicating that missing data are nonignorable, the interpretation of related findings should take missingness into account. No interim analyses other than monitoring of demographic data are planned.

Continuous variables will be summarized according to intervention groups at baseline, if applicable, and end of trial using arithmetic or geometric means, standard deviations, ranges, and interquartile ranges as appropriate. Change from baseline will be summarized descriptively accompanied by its 95% CI. In descriptive summaries, last observation carried forward (LOCF) will be employed to impute missing values. Categorical variables at baseline and end of trial (if applicable) will be summarized as absolute number and proportion of subjects (%) according to intervention groups.

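### For 24-h ambulatory BP, the pattern-mixture sensitivity analysis cannot estimate the pattern-by-time interactions it lists, so it cannot show whether dropout is non-ignorable

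*Protocol article*

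**What the plan says.** All references are to the Protocol article.

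- **Method.** Statistical considerations names one missing-data sensitivity analysis: "Incomplete data will be explored in sensitivity analyses by pattern mixture model". Its purpose is stated next: "This procedure will describe whether there is an interaction between the main missing patterns and other variables (e.g., group, time, group by time". The list is illustrative and goes on to BP status and BP status by group.
- **Patterns.** Two are expected, based on "an indicator of completers versus non-completers (defined as randomized subjects without 12-week data". Further grouping by reason for withdrawal is left open, and reasons are to be recorded case by case. If identifiable patterns point to non-ignorable missingness, interpretation is to allow for it.
- **Outcome schedule.** Primary outcome states: "The primary study outcome is systolic BP assessed by 24 h ambulatory BP monitoring measured before and after three months of intervention". Values are "aggregated as group means at baseline and 12 weeks (trial end". Table 3 marks ambulatory BP at t0 and t5 only.
- **Week-6 visit.** Data collection says that all variables are taken at baseline and completion, "whereas endothelial function, self-reported physical activity and handgrip strength are additionally assessed at the 6th week of intervention". Ambulatory BP is not among these.
- **Dropouts.** Under Outcomes, "research personnel use contact information to invite such individuals to undergo the end-study outcome assessments".
- **Other uses of incomplete data.** Last observation carried forward is confined to descriptive summaries. The per-protocol set contains completers only and is not presented as a missing-data analysis.

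**The concern.** A pattern × time term asks whether non-completers change differently from completers. A pattern × group × time term asks whether the treatment effect differs between them. Both need post-baseline outcomes in non-completers. For ambulatory BP the plan's own definition rules these out: a participant without 12-week data has only a baseline reading.

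The text nevertheless proposes to look for these interactions in the observed data and to judge non-ignorability from what is found. For the primary outcome of a trial that the Discussion calls confirmatory, with an intention-to-treat analysis of everyone randomized, that leaves no planned way to gauge how sensitive the result is to informative dropout.

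**Working it through.** **Inputs.** From Sample size: 184 participants, 22 allowed for dropout (stated rate 10–15%), SD 6.0 mmHg, intraclass correlation 0.1, two-sided 0.05, power 0.79 and 0.92 for 2.5 and 3.0 mmHg. Allocation is 1:1 (Abstract, Methods). Assumption: the 22 split evenly, 11 per arm.

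**1. The plan's own figures.** 22/184 = 12.0%, inside the stated 10–15%. With 184 − 22 = 162, or 81 per arm, and SD 6.0 × √(1 − 0.1) = 5.69, the standard error of the difference is 5.69 × √(2/81) = 0.894 mmHg. Power from the noncentral t distribution is 0.793 for 2.5 mmHg and 0.915 for 3.0 mmHg, which reproduces 0.79 and 0.92. The sample size is not affected by this point.

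**2. Which terms can be estimated for ambulatory BP.** Code G = 1 for exercise, T = 1 for 12 weeks and P = 1 for non-completer. The full model has 8 columns: 1, G, T, G×T, P, P×G, P×T, P×G×T.

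| | Baseline | 12 weeks |
|---|---|---|
| Completers, each arm | observed | observed |
| Non-completers, each arm | observed | empty by definition |

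Over two arms this gives 8 cells, of which 6 are observed. P×T equals 1 only for a non-completer at 12 weeks, and there is no such row, so P×T and P×G×T are zero throughout. With 92 per arm there are 2 × (81 × 2 + 11) = 346 rows, and the design matrix has rank 6 against 8 columns.

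- Adding BP status, BP status × group, and their products with pattern gives 12 columns and rank 10. The same two columns are empty.
- P, P×G and the BP-status terms can be estimated. Non-completers have baseline values only, so the terms involving pattern compare baseline BP between patterns.
- In the primary model (final values adjusted for baseline), non-completers contribute no outcome row, so no pattern term can be estimated.
- Splitting non-completers by reason for withdrawal does not help, because every subgroup lacks 12-week data. Dropouts who accept the final visit have 12-week data and are no longer non-completers.

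**3. Can the analysis detect informative dropout?** One data set was simulated with 92 per arm, 11 non-completers per arm and a treatment effect of −3 mmHg. The non-completers' unseen 12-week values in the exercise arm were then shifted by 0, 5 or 10 mmHg. The estimated group × time effect was −3.567 without the estimable pattern terms and −3.301 with them, identical for all three shifts. The shifted values never enter the data, so this outcome is unavoidable.

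**4. How far the result could move.** Let f be the fraction without 12-week data, equal in both arms, and δ the treatment effect in non-completers minus that in completers. Then

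overall effect = (1 − f) × completer effect + f × (completer effect + δ) = completer effect + f × δ.

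The documents give no δ, so the values below are assumptions.

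| f | δ = 2.5 | δ = 5 | δ = 10 mmHg |
|---|---|---|---|
| 0.10 | 0.25 | 0.50 | 1.00 |
| 22/184 = 0.12 | 0.30 | 0.60 | 1.20 |
| 0.15 | 0.38 | 0.75 | 1.50 |

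**5. Outcomes with a week-6 value.** With three timepoints, and non-completers seen at baseline and week 6, the model without BP status has 12 columns and rank 10. The pattern × week-6 terms can be estimated; the pattern × week-12 terms remain empty.

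**The case against.** Every pattern-mixture model has components that the data do not identify, and each needs a restriction from outside. An article may name the model class and leave the restriction to a statistical analysis plan, which is not shown here. The list of interactions is only illustrative, and several of its terms can be fitted. The paragraph covers incomplete data in general, including endothelial function, handgrip and physical activity, where the week-6 visit supplies some post-baseline information. Reasons for withdrawal are also to be documented.

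Much of this stands. A reader might infer that the model cannot be fitted at all. The documents do not support that: the failure is confined to the time-related pattern terms, and it is complete only for outcomes measured at two timepoints. A reader might also infer that the trial will report a robustness it never tested. The text does not say so. It speaks of exploring and describing, and nowhere says that the absence of an interaction will be presented as reassurance.

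What does not stand is the reply that only detail has been left out. The article says how non-ignorability is to be recognised, namely from interactions and identifiable patterns in the data. For ambulatory BP that route is closed, and documented withdrawal reasons cannot by themselves put a size on the effect.

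**Conclusion.** The point holds for 24-h ambulatory BP and should be fixed. The two listed interactions that bear on informative dropout have no data, and the fitted pattern terms describe baseline differences only.

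The possible movement is moderate: 0.30 to 1.20 mmHg at 12% missing, and 0.25 to 1.50 mmHg across 10–15%, against design differences of 2.5 and 3.0 mmHg. This rests on assumed δ values of 2.5 to 10 mmHg and equal missingness in the arms. It also treats planned dropout as missing 12-week data. Because dropouts are invited back, 22 is a planning figure and the number without 12-week data may be smaller.

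It would be going too far to call the primary result biased. The primary estimate and test do not depend on this model, and non-identification in a sensitivity analysis is not evidence of bias.

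**What to change.** Keep the pattern-mixture framework and state an explicit identifying assumption for missing 12-week 24-h systolic BP. One suitable form is delta-adjusted multiple imputation:

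- Impute from arm, centre and baseline 24-h systolic BP.
- Add a delta to the imputed values, first in the exercise arm alone and then in both arms.
- Report the delta at which the primary conclusion changes.

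The documents give no delta range, so the sponsor should choose and justify one. Other explicit restrictions would also repair the defect.

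Weekly pre-session BP may serve as an auxiliary variable, with two caveats. It stops when the participant withdraws. It is also not measured alike in the two arms: under Hypertension management, exercise participants with high readings may be re-measured after a short walk and rest.

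Describe the pattern × group and BP-status terms as baseline comparisons of completers and non-completers, not as a test of non-ignorability. State that time-related pattern terms apply only to outcomes with a week-6 value, and only up to week 6.

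The cost is a few sentences and a little extra programming. No new data are needed, and the primary analysis and sample size are unchanged.

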### Monitoring

#### Data monitoring

The HAEL Study does not have a data monitoring committee due to limited resources. We reason this committee would not be mandatory due to the characteristics of interventions and outcomes, despite its highly value for the overall quality of the trial.

#### Harms

The identification, possible solutions, and documentation of adverse events are based on a study management algorithm requested and approved by the Institutional Review Board from the coordinator center.

#### Auditing

If necessary, auditing will be conducted by the Hospital de Clínicas de Porto Alegre through defined protocols implemented by an independent monitoring team adjunct to the IRB structure.

### Ancillary, post-trial care and harm from trial participation

After enrollment in the HAEL Study, each participant receives a brief report of health status prepared by a researcher not involved in intervention implementation and data assessments. If requested, punctual tests information can be given to participants for treatment matters. For harms suffered during trial enrollment related to the study (after adjudication by the committee), we planned contingency actions to assist the participant through care provided either at primary health care units or at the Hospital de Clínicas de Porto Alegre (tertiary care). Finally, the HAEL Study staff has Basic Life Support training and an algorithm for major adverse events is available if necessary.

### Dissemination policy

We aim to disseminate the methods and findings of the HAEL Study to as many stakeholders as possible. Therefore, our dissemination plan after trial completion encompasses the following: (1) breakfast meeting with study participants by which we will present a layman-friendly explanation about the study design, findings, and interpretation; (2) press releases written by journalists and directed towards the general public, and (3) scientific manuscripts. For the latter, criteria for authorship on HAEL Study publications will adhere to the recommendations by the International.

Committee of Medical Journal Editors [37] and those defined by the destination journals. Because we have established a relatively large multi-author group, some publications will carry authorship by a group name designated the HAEL Study Group. When submitting a manuscript authored by HAEL Study Group, byline authors will be mostly defined by full-time equivalents of workload in trial activities. To this end, we do conduct monitoring of all investigators workload on a weekly basis. To ensure reporting completeness, manuscripts written by the HAEL Study Group must adhere to the CONSORT Statement [38], or, if applicable, more suited reporting guidelines.

## Discussion

The HAEL Study presents features which are relevant to be highlighted. First, we established our research question towards the elderly population. Beyond a justification of scantiness of large exercise studies in samples exclusively composed by older individuals, elderlies represent our population of interest primarily because they yield a high prevalence of hypertension and present an exponentially increased risk of death [2]. Therefore, assessing the efficacy of lifestyle interventions that may positively influence BP control in this population is desirable, particularly because older individuals are common polypharmacy users and present reductions in both physical and psychological and/or cognitive domains. Second, we chose to implement a combined training intervention as the candidate method to provide superior effects in BP reduction, vascular adaptation, and functional measures. Importantly, this type of intervention has been recommended in several position stands of exercise to maximize health benefits because both cardiovascular and neuromuscular stimuli occur in parallel. Moreover, we simplified the choice of aerobic and resistance exercises so that the program may be more feasibly implemented in public health settings or low-resource scenarios. Third, we designed the comparator intervention to minimize possible differences due to participation (Hawthorne) effects as well as provide participants with information on varied topics related to hypertension management. Although the interventions differ in weekly frequencies, equating the frequencies of both programs in three times a week would make education meetings more repetitive and probably reduce attrition rates.

Finally, we point out that the HAEL Study is confirmatory trial by nature. Therefore, we have designed this trial establishing methodological standards as high as possible for both outcome measurements and trial management. In this regard, we emphasize some aspects such as the (i) use of 24-h ambulatory systolic and diastolic BP, which is scarcely available from previous trials; (ii) a standardized management plan for participants with uncompensated BP; and (iii) open research practices that will likely make the trial more useful and reproducible.

## Abbreviations

BP: Blood pressure
FMD: Flow-mediated dilatation
IPAQ: International Physical Activity Questionnaire
IRB: Institutional review board
ITT: Intention-to-treat
LOCF: Last observation carried forward
MOP: Manual of operating procedures
QoL: Quality of life
SPPB: Short Physical Performance Battery
VO2peak: Peak oxygen consumption
